### Dosing, adverse effects, and contraindications

To understand the optimal dosing or adverse events associated with the FES, certain studies have shown that a minimum of 20 FES sessions were needed to detect a change in function, and 40 FES sessions were needed to see a change in the quality of life. Regarding the tolerability

and safety of the FES, no significant adverse events have been noted. Common mild adverse events include redness below the area of the electrodes, which typically dissipates within 24 hours, and occasional muscle fatigue or soreness, which also typically resolves without intervention within 24 hours.

The use of FES in a therapeutic setting is associated with certain contraindications, which include metal implants at the stimulation site, pacemakers, open wounds or rash at the electrode placement site, and uncontrolled autonomic dysreflexia. The FES target muscles have to be accessible for placement of the stimulation electrodes – for example, transcutaneous FES can be delivered with a greater level of specificity when the target muscles are more superficial (e.g., flexor carpi ulnaris, flexor carpi radialis), while for deeper muscles, eliciting an isolated contraction without stimulating the overlying muscles (e.g., flexor digitorum profundus) might be more challenging. Certain muscles, such as the iliopsoas, cannot be stimulated using surface electrodes due to their anatomical location. Furthermore, the degree of lower motor neuron injury or nerve root damage of the stimulated muscle must not be significant. Finally, the patient must be cognitively able to follow the instructions and actively participate in the therapy process for the maximal therapeutic benefit from the FES.

While the FES devices are portable, a home-based study to examine efficacy and tolerability is essential as all compliance will be monitored and intervention delivered under observation by a physiotherapist or a trained investigator. Therefore, besides investigating the feasibility and efficacy of FES, we will develop a prototype for a home-based device with a cast-molded personalized Mask on a 3D printed mold and programmable stimulator to enable self-administration.

#### **4. Study Objectives**

Based on the Facial Feedback Hypothesis, our overarching goal is to test the FES of the Duchenne muscles in participants with MDD in a randomized controlled trial (RCT). The primary objectives of the trial will be to estimate the feasibility, tolerability, and safety outcomes of recruitment, dropout, data completion, and protocol compliance rates, and the number and nature of adverse events and serious adverse events, to evaluate patient experience with the FES. We aim to enhance positive emotions and treat MDD by developing a prototype for a home-based device with a personalized Mask. In this RCT, 20 participants with non-treatment resistant MDD will be randomized to receive twenty 60-minute sessions (15 min for preparations and 45 min for stimulation) of FES vs. sham-FES over 4 weeks (20 treatments).

#### **Primary Objectives**

**Aim 1:** to evaluate the feasibility of the FES for MDD

**Hypothesis 1a:** the overall dropout and protocol compliance rates will not differ significantly between participants randomized to FES or sham-FES.

**Hypothesis 1b:** the overall number of adverse events (AEs) and serious adverse events (SAEs) will not differ significantly between participants randomized to FES or sham-FES.

**Hypothesis 1c:** the nature of AEs and SAEs and the patient experience will not have a significant impact on the dropout and protocol compliance rates.

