### **5.3. Method of Recruitment**

The single study center will be the Interventional Psychiatry Program at St. Michael's Hospital, Unity Health Toronto (SMH, UHT). The subjects will be recruited from the Interventional Psychiatry Program at St. Michael's Hospital, Unity Health Toronto. The target recruitment rate is a total of 20 subjects recruited over 6 months. Considering our prior experience with this type of study, we do not anticipate any significant compliance issues. We note that the 5 sessions per week proposed here exceeds the schedule in the preliminary study by 2 sessions per week with the presence of a sham arm; we have included a conservative 15% dropout rate in our sample size calculations. However, a 5 session per week schedule is well tolerated in rTMS for MDD and in FES for stroke rehabilitation. Notably, since the intervention includes monitored home-based visits, treatment adherence will be known with 100% accuracy.

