**Table 1: Study Schedule**

## 6.2. Randomization and Blinding

Participants will be randomized in a 1:1 allocation to receive FES (active pattern) or FES (sham pattern). Block randomization will be computer-generated, and the samples will be stratified for sex, given the potential differences in response and tolerability in these groups. A biostatistician will generate the randomization schedule, to be administered by a research assistant who is not associated with the study and instructed not to divulge group assignments to the participants to allow for concealment.

Participants and most study staff will be blinded. Only the physical therapist will need to monitor the participant. Measures taken to prevent functional unblinding include sensory and non-patterned sham and delivering automated messages to both active and sham groups. We will also evaluate each participant's ability to discriminate what treatment they received after each session to assess blinding effectiveness.

We will randomize subjects to study arms (20 days active or 20 days sham) using a secure online randomization module on REDCap. The block size will be fixed, and study personnel will be blinded to the randomization block size. An independent assistant, external to the study, will manage the randomization of subjects. The subject number and treatment code will be assigned

after the subject details have been obtained. Based on this information, the independent assistant will assign a unique subject number and treatment code, which will dictate the treatment assignment for the subject. The patterns will be pre-programmed into the take-home device by the biomedical team.

An unblinded code sheet that matches these stimulation codes to the treatment arm will be kept by an external coordinator and will not be available to the study coordinator or research assistants. The unblinded code sheet will have the following information:

1. The initial identifier codes for all potential participants
2. Stimulation code: 6-digit numerical code for the stimulation session
3. Condition number: Numerical code for the condition
4. Condition name: Name of the condition

A copy of this code sheet with the condition name removed will be provided to the study coordinator and research assistants. These linked codes ensure that the study coordinator and research assistants are kept blinded to the type of treatment each participant will receive.

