### **14. Data Analysis**

#### **14.1. Sample Size Considerations and Study Feasibility**

For this pilot feasibility trial, we aim to recruit 20 participants in total.

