## **14.2. Clinical Outcomes Analysis**

We are primarily interested in precise estimates of tolerability, outcome variability, and preliminary effectiveness of FES compared to sham FES in patients with MDD that will aid in the planning of a larger, sufficiently powered efficacy trial.

Initial analyses will summarize socio-demographic and clinical characteristics by treatment group. Primary analyses will be performed on the modified intention-to-treat (ITT) population, including all randomized participants that received at least one FES treatment. The feasibility outcome defined as overall dropout rates will be summarized using descriptive statistics such as counts and percentages. Feasibility analyses will report feasibility outcomes using descriptive statistics with counts and proportions for categorical data and means and standard deviations or median and interquartile range, as appropriate, for continuous data. The proportion lost to follow-up will be estimated along with a 95% confidence interval. The lower 95% confidence limit should be at least 90% to proceed. The proportion compliant with the protocol, including treatment compliance as well as study completion and complete data on clinical outcomes will be estimated with 95% confidence interval. For validity to be fairly high, the lower 95% confidence limit should be >90%. The blinding index proposed is scaled to an interval of -1 to 1, 1 being a complete lack of blinding, 0 being consistent with perfect blinding and -1 indicating opposite guessing, which may be related to unblinding.

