The preliminary effectiveness analysis will report the between group difference in change from baseline to treatment 20 in the HAM-D-17 and its 95% confidence interval, using analysis of covariance (ANCOVA), with 20 treatment HAM-D-17 as the outcome and baseline HAM-D-17 and stratification variables (sex) as covariates. We will also report estimates for standard deviation of HAM-D-17 score and within-person correlation between baseline and follow-up HAM-D-17 scores. A similar approach will be used for all other continuous variables for secondary outcome measures (e.g., QIDS-SR, GAD-7, etc). Differences between groups in dichotomous outcomes (e.g., response, remission, adverse effects) will be described using an odds ratio and 95% confidence interval. To explore the sustainability of the treatment effect, we aim to also report changes of HAM-D-17 scores during the month after 20 treatments. The success of blinding of patients will be assessed by computation of Bang's blinding index. Sex and gender stratified analysis will be carried out.

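### Primary Hypotheses 1a to 1c are worded as absence of a significant difference with no margin, which about 10 participants per arm cannot turn into evidence that FES and sham are similar

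*Protocol*

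**What the plan says.** Section 4 of the protocol (Primary Objectives) sets three hypotheses under Aim 1. Hypothesis 1a is that "the overall dropout and protocol compliance rates will not differ significantly between participants randomized to FES or sham-FES". Hypothesis 1b is that "the overall number of adverse events (AEs) and serious adverse events (SAEs) will not differ significantly between participants randomized to FES or sham-FES". Hypothesis 1c predicts that the kind of events and the patients' experience will have no significant effect on dropout and compliance. None of the three comes with a margin, and no margin appears elsewhere.

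On size, section 14.1 says "For this pilot feasibility trial, we aim to recruit 20 participants in total" and gives no power, precision target or significance level. Section 6.2 fixes 1:1 allocation, stratified by sex, so about 10 per arm. Section 5.3 states that "we have included a conservative 15% dropout rate in our sample size calculations", though no calculation is shown.

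The opening of section 4 describes the primary objectives as estimating these outcomes, and section 14.2 says the main interest is in precise estimates for planning a larger trial. Its plan for dropout is that "The feasibility outcome defined as overall dropout rates will be summarized using descriptive statistics such as counts and percentages". It adds 95% confidence intervals for single proportions (loss to follow-up, compliance). Its between-arm statement is: "Differences between groups in dichotomous outcomes (e.g., response, remission, adverse effects) will be described using an odds ratio and 95% confidence interval".

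**The concern.** A hypothesis of no significant difference is met by failing to reject. In a small trial that happens mainly because there is little information, whatever the true difference. Without a margin, nothing separates arms that are similar from arms that are too small to compare.

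At stake is what the trial may conclude on its primary objective. If dropout were considerably higher on active FES than on sham, Hypothesis 1a would still usually come out as stated. A later reader planning the larger trial could then take tolerability as comparable when the data leave the question open. The hypotheses also ask for a significance verdict that the analysis section does not plan and that does not fit the declared aim of estimation.

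**Working it through.** **Plan's own figure.** The total of 20 cannot be reproduced, because section 14.1 gives no inputs.

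**Inputs.** From the protocol: 10 per arm (20 at 1:1) and 15% dropout as the reference rate (section 5.3). Assumptions: two-sided level 0.05, in line with the 95% intervals in section 14.2; Fisher's exact and Pearson chi-square as the two obvious tests, since none is named; 15% taken as the rate in the better arm; a range of true rates in the other arm.

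**Smallest splits that reach significance (Fisher).**
- 0/10 v 4/10: p = 2 × C(10,4)/C(20,4) = 2 × 210/4845 = 0.087, not significant.
- 0/10 v 5/10: p = 2 × C(10,5)/C(20,5) = 2 × 252/15504 = 0.033, significant.
- 1/10 v 6/10: p = 0.057, not significant. 1/10 v 7/10: p = 0.020, significant.

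**Probability of a non-significant result.** With x and y the dropouts in the two arms,

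P(non-significant) = 1 − Σ Bin(x; 10, p₁) × Bin(y; 10, p₂), summed over all (x, y) whose test gives p ≤ 0.05.

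| True dropout | Fisher | Chi-square |
|---|---|---|
| 15% v 30% | 96.6% | 91.0% |
| 15% v 40% | 90.5% | 80.4% |
| 15% v 50% | 80.1% | 65.1% |
| 15% v 60% | 65.1% | 46.5% |
| 10% v 40% | 84.8% | 70.9% |
| 10% v 50% | 70.5% | 52.9% |

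**Adverse events (rates assumed).** If 0% v 30% of participants have an SAE, Fisher needs at least 5 of 10 in the second arm. P(X ≥ 5) for Bin(10, 0.30) is 0.150, so 85% of trials are non-significant. For Poisson event counts with means of 1 v 2 per participant, an exact conditional test is non-significant in 1 − 0.374 = about 63%; overdispersion would raise this.

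**What the data can say instead.** Newcombe 95% interval for 1/10 v 1/10: the Wilson limits for 1/10 are 0.018 and 0.404, so the half-width is √[(0.100 − 0.018)² + (0.404 − 0.100)²] = 0.315, that is about -32 to +32 points. For 4/10 v 1/10 (Fisher p = 0.30) the interval is -8 to +60 points.

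**Could a margin be tested?** With 15% true dropout in both arms, one-sided 0.025 and 80% power, n per arm = (1.96 + 0.84)² × 2 × 0.15 × 0.85 / margin². This gives 23 per arm for a 30-point margin, 51 for 20 points and 201 for 10 points. With 10 per arm, none of these is within reach.

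**Empty cells.** At 15% in both arms, the chance that at least one arm has 0 or 10 events is 1 − (1 − 0.85¹⁰ − 0.15¹⁰)² = 35.5%. An uncorrected odds ratio then has no finite 95% interval; a Newcombe risk difference still does (0/10 v 0/10: about -28 to +28 points).

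**The case against.** The best defence is that this is leftover wording beside an estimation plan. Section 14.2 names no between-arm test of dropout, compliance or adverse events. Its stated criteria are confidence limits on single proportions, not a comparison of FES with sham. That stands, and it limits the practical harm. It does not remove the point: the primary hypotheses still ask for a significance verdict, and section 14.2 supplies no between-arm estimate for dropout or compliance in its place. Its list of dichotomous outcomes is given as examples, so dropout might be read into it, but dropout is handled separately and descriptively.

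The size also depends on the test. Fisher is conservative; chi-square figures are lower, and at 15% v 60% chi-square would find the difference slightly more often than not. A non-significant result is therefore likely, not guaranteed.

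Three stronger readings are tempting and not supported:
- A reader might infer that the protocol declares the arms equal if no significant difference is found. It says only that they will not differ significantly; no section states how that result will be read.
- A reader might infer that an excess of adverse events would be hidden. Number and nature of events are primary outcomes (section 8.1), events are collected daily and graded individually (section 11), and their frequency can trigger a safety review (section 10.4). Reporting does not depend on significance.
- A reader might infer that the odds ratio in section 14.2 is an error. It is a descriptive choice, and the handling of empty cells or of event counts may be left to the statistical analysis plan.

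**Conclusion.** The point holds for the wording of Hypotheses 1a to 1c. They are framed as absence of a significant difference or impact, without a margin, at a size where that result is likely under large true differences: about 80% to 90% of trials (Fisher) or 65% to 80% (chi-square) at 15% v 40% to 50% dropout. Such a result cannot support similar dropout, compliance or adverse events. The wording also conflicts with the aim of estimation in sections 4 and 14.2.

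These figures assume a two-sided 0.05 level, 10 per arm and the true rates shown. Sex-stratified blocks may leave the arms slightly off 10 and 10, which does not alter the conclusion. Because the planned analysis is mainly descriptive, the defect lies in what the primary hypotheses claim, not in a faulty test.

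**What to change.** Reword Hypotheses 1a and 1b as estimation objectives: report the between-arm difference with a 95% confidence interval, for example a Newcombe risk difference, for dropout, for protocol compliance, and for the percentage of participants with at least one AE and with at least one SAE. Make 1c descriptive. Add a sentence that a non-significant difference will not be read as similarity. In section 14.2, add the between-arm difference for dropout and compliance. The odds ratio may stay as a descriptive summary; a risk difference beside it gives an interval when a cell is empty.

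The cost is wording and one further statistic in a standard table, with no change to design or sample size. The stated claim becomes weaker: the trial would report how large a difference remains possible and would no longer predict that there is none. Keeping a claim of similarity would need a justified margin, and 20 participants could not test one of 30 points or less at 80% power under the assumptions shown.

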## Secondary Objectives:

**Aim 2:** to evaluate the efficacy of FES for MDD

**Hypothesis 2:** over 4 weeks, participants randomized to FES will have a significantly larger reduction in the 17-item Hamilton Depression Rating Scale (HAM-D-17) and self-rated 16-item Quick Inventory of Depressive Symptoms (QIDS-SR-16) total score than those randomized to sham-FES.

**Aim 3:** to evaluate the response and remission rates; the impact of FES on insomnia, quality of life, and function; and sustainability of effects up to 4 weeks (28 days) after completion of the intervention.

**Hypothesis 3:** over 4 weeks, participants randomized to FES will have a significantly larger reduction in the total score of Generalized Anxiety Disorder-7 Scale (GAD-7), World Health Organization-5 Well-Being Index (WHO-5), and Pittsburgh Sleep Quality Index (PSQI) than those randomized to sham-FES.

## 5. Subject Selection and Recruitment

### 5.1. Inclusion and Exclusion Criteria

#### Inclusion Criteria

Patients will be included if they:

1. Meet the DSM-5 (67) criteria for unipolar MDD with a current MDE without psychotic features, with  $\leq 2$  failed treatment trials (non-treatment-resistant depression), as determined by a physician and validated by a MINI (68) done by a trained research assistant.
2. Have no change in the medication regimen or other forms of treatments (e.g., psychotherapy) for at least 4 weeks (28 days) prior to beginning the study, during the 20-session treatment period, and the 4-week post-treatment observation period. This will be established through self-report, in combination with the ATHF (69, 70) filled out by the participant.
3. Have an MDD diagnosis as confirmed by the MADRS (71) score of  $\geq 6$
4. Are above 18 years of age.

#### Exclusion Criteria

Patients will be excluded if they:

1. Have a history of epilepsy or seizures

2. Have any paralysis of facial nerves
3. Have metallic implants in the mouth or metal braces near the potential sites of electrical stimulation, and any type of implanted electronic devices (insulin pump, pacemaker...)
4. Have current fibromyalgia or currently receiving or have received rTMS within the last month (28 days) before screening
5. Have any past or current symptoms of mania, hypomania, mixed episodes, psychotic disorders, active substance abuse, or dependence (excluding nicotine and caffeine), which will be confirmed on the MINI done by a trained research assistant
6. Have current suicidal intent or plan as demonstrated by a score of  $\geq 2$  on MADRS item 10.
7. Are unable to understand instructions in English
8. Are unable to produce the “Duchenne marker” expression (see “Procedures” for details) with FES, secondary to any type of neurological condition or previous botulinum toxin treatments of facial muscles
9. Pain in the body part being tested (measured and/or stimulated)
10. Skin lesion at a site of stimulation electrodes or motion sensors
11. Any type of bone fracture
12. Females who are pregnant or planning to become pregnant throughout the duration of the study.
13. Active deep vein thrombosis
14. Cancer or radiation in the past 6 months
15. Uncontrolled autonomic dysreflexia
16. Orthostatic hypotension
17. Botulinum toxin injection into muscles targeted by the stimulation in the past 6 months

**Justifications for any exclusions based on race, gender, or ethnicity:** non-English speaking individuals are excluded because the ability to accurately and completely communicate study information, answer questions about the study, and obtain consent are necessary.

## **5.2. Concomitant Medications (CONMED)**

Participants will be asked to remain on stable dosages of concomitant psychotropic medications. Changes to treatment regimens or the introduction of psychotherapy, however, will not be permitted during the acute intervention phase of the trial (4-week/ 28 days), 4 weeks (28 days) before the start of the trial, and during the 4-week (28 days) follow-up period. If changes to treatment regimens or the introduction of psychotherapy are determined to be required as per the patient's standard of care, the required changes will be made, and the participant will be withdrawn from the study.

### **5.3. Method of Recruitment**

The single study center will be the Interventional Psychiatry Program at St. Michael's Hospital, Unity Health Toronto (SMH, UHT). The subjects will be recruited from the Interventional Psychiatry Program at St. Michael's Hospital, Unity Health Toronto. The target recruitment rate is a total of 20 subjects recruited over 6 months. Considering our prior experience with this type of study, we do not anticipate any significant compliance issues. We note that the 5 sessions per week proposed here exceeds the schedule in the preliminary study by 2 sessions per week with the presence of a sham arm; we have included a conservative 15% dropout rate in our sample size calculations. However, a 5 session per week schedule is well tolerated in rTMS for MDD and in FES for stroke rehabilitation. Notably, since the intervention includes monitored home-based visits, treatment adherence will be known with 100% accuracy.

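### The 15% dropout allowance in section 5.3 cannot be traced to any calculation, and neither it nor a sample of 20 is compatible with the 90% proceed limit in section 14.2

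*Protocol*

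**What the plan says.** Section 5.3 of the protocol notes that the session schedule is denser than in the preliminary study and that there is now a sham arm. It then says: "we have included a conservative 15% dropout rate in our sample size calculations". The same section gives the recruitment target: "The target recruitment rate is a total of 20 subjects recruited over 6 months".

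Section 14.1 is the section headed for sample size. It consists of one sentence: "For this pilot feasibility trial, we aim to recruit 20 participants in total". Section 4 uses the same number for those randomised: "20 participants with non-treatment resistant MDD will be randomized to receive twenty 60-minute sessions". The protocol states no evaluable number, inflation step, power, effect size, planning standard deviation or target interval width.

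Section 14.2 opens with an aim: "We are primarily interested in precise estimates of tolerability, outcome variability, and preliminary effectiveness of FES". On feasibility it says: "The proportion lost to follow-up will be estimated along with a 95% confidence interval". The next sentence is the decision rule: "The lower 95% confidence limit should be at least 90% to proceed". A parallel rule follows for protocol compliance, which there includes treatment compliance, study completion and complete clinical data. Its lower 95% limit should exceed 90%.

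**The concern.** There are two linked difficulties. First, section 5.3 reports a step in a calculation that the protocol's own sample-size section does not contain. A reader cannot tell whether 20 is the number before or after the allowance for dropout.

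Second, the dropout allowance and the proceed rule are parts of one plan and do not fit together. Feasibility is the primary outcome, and the rule in section 14.2 is the stated condition for going on. If the rule cannot be met at this sample size, it cannot inform that decision. The investigators would have to stop a trial that retained everyone, or set their own criterion aside after seeing the data.

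**Working it through.** **Inputs.** Total recruited and randomised: 20 (sections 4, 5.3, 14.1). Dropout allowance: 15% (5.3). Decision limit: lower 95% confidence limit of at least 90% (14.2). The protocol does not name an interval method. Exact (Clopper-Pearson) two-sided intervals are used here, with Wilson as a check.

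**1. Can 20 be reproduced?** Not from a power or precision formula, because the protocol gives no inputs for one. Only the dropout step can be tried, using N = evaluable/(1 − dropout):

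- 17 evaluable: 17/0.85 = 20.0, which matches the stated total.
- 20 evaluable: 20/0.85 = 23.5, so 24, which does not match.

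The stated 20 is thus consistent with an unstated evaluable target of 17. The documents neither confirm nor exclude it.

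**2. Does the allowance fit the proceed rule?** 20 × 0.85 = 17 retained and 3 lost.

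| Reading of the rule | Observed | Exact 95% interval | Lower limit at least 90%? |
|---|---|---|---|
| On retention | 17/20 = 85% | 62.1% to 96.8% (Wilson 64.0% to 94.8%) | No |
| Literally, on loss | 3/20 = 15% | 3.2% to 37.9% | No |

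The literal reading would also reward loss, so the sentence looks like a slip of direction. The result does not depend on which reading is taken.

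**3. Is the dropout figure the cause?** With nobody lost, the exact lower limit is 0.025^(1/n):

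- n = 20: 0.025^(1/20) = 83.2% (Wilson 83.9%; one-sided 95% exact limit 0.05^(1/20) = 86.1%).
- n = 24: 85.8%.
- n = 35: 0.025^(1/35) = 89.997%, just short.
- n = 36: 90.3%, the first perfect result to pass.

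Wilson needs 35 of 35, and a one-sided exact limit needs 29 of 29. The rule is therefore out of reach at n = 20 whatever dropout is assumed. The same holds for the limit above 90% on compliance and completion. The modified ITT population can only make the denominator smaller.

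**4. What would a criterion on the observed proportion do?** If true dropout were 15%, the chance of no loss among 20 is 0.85^20 = 3.9%. The chance of at most 2 lost (18 of 20, observed 90%) is 40.5%. The chance of exactly 3 lost is 1140 × 0.15³ × 0.85^17 = 24.3%, so the chance of at most 3 lost (17 of 20, observed 85%) is 40.5% + 24.3% = 64.8%. Both thresholds are attainable at n = 20, but an observed 90% would still sit awkwardly with a 15% allowance.

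**5. Expected precision (assumption-based).** The protocol gives no planning standard deviation. As an assumption, take the pilot's standard deviation of HAM-D change, 5.26 (section 3), as the ANCOVA residual standard deviation. With 17 completers and four fitted parameters (intercept, arm, baseline, sex), residual df = 17 − 4 = 13 and t = 2.16. The half-width is 2.16 × 5.26 × √(2/8.5) = about ±5.5 HAM-D-17 points. It scales in proportion to the assumed value.

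**The case against.** The strongest reply is that this is a pilot whose size was set pragmatically, and that section 5.3 calls 15% conservative and says no significant compliance problem is expected. On that view 15% is a safety margin and 85% retention is not a forecast, so it should not be held against a go criterion. This is fair as far as it goes, and it rules out saying that the plan predicts its own failure. It does not rescue the rule, which fails at n = 20 with no dropout at all.

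A reader might infer that the 15% was never applied, or that 24 participants are needed. The documents do not support either. Because 17/0.85 = 20 exactly, the allowance may well be in the total, and nowhere does the protocol describe 20 as an evaluable number.

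A reader might also infer that section 14.2 promises a precision that 17 completers cannot give. It states an aim and names no width, and it commits to reporting confidence intervals and variability. There is no stated target to miss. Dropout also need not mean no outcome, because section 6.3 allows people who stop early to be asked back for assessments.

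Finally, a simple Wald interval has zero width at 20 of 20 and would pass. That reflects a known failure of the Wald interval at the boundary and does not show that the rule works. One loss already brings its lower limit to 85.4%.

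**Conclusion.** The point holds in this form. The dropout allowance in section 5.3 refers to calculations that the protocol does not show, so it cannot be verified; no arithmetic error is demonstrated. Separately, the allowance and the proceed rule are incompatible: 85% retained has an exact lower limit of 62.1% against a required 90%, and the literal reading on loss fails as well. The deeper cause is the pairing of a 90% lower limit with 20 participants, since perfect retention reaches only 83.2%. Changing the 15%, or recruiting 24, would not cure it.

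The conclusion assumes a two-sided exact interval. Wilson and one-sided exact limits lead to the same result at n = 20. The precision figure of ±5.5 points is illustrative, rests on a borrowed standard deviation, and is not part of the defect.

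**What to change.** **Sections 5.3 and 14.1.** Keep 20. If 17 was the intended evaluable number, say so in both places: 20 randomised; with 15% dropout, 17 evaluable. If no calculation was made, delete the reference to one and give the pragmatic basis for 20.

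**Section 14.2.** Restate the proceed rule on the proportion retained, and the companion rule on the proportion compliant and complete. For each, choose a threshold that 20 participants can meet and that is compatible with the 15% allowance. One option is a criterion on the observed proportion, reported with its exact 95% confidence interval. Name the interval method.

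**Optional.** Add the expected precision for the HAM-D-17 difference, about ±5.5 points with 17 completers, with its assumptions (residual standard deviation 5.26, 13 residual df).

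**Cost.** A few sentences of protocol wording. No added participants, and no change to treatment or data collection. The stated criterion, and any stated precision, will look less favourable than the present text suggests.
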